
### Trial design

Prospective randomized open phase III non-inferiority trial in patients with cT1bT2N0 [50] papillary thyroid carcinoma comparing: total thyroidectomy alone (experimental group) versus total thyroidectomy with prophylactic neck dissection (PND) (reference group).

*Group 1 (reference group)*: total thyroidectomy with bilateral prophylactic central compartment (level VI) neck dissection

*Group 2 (“experimental” group)*: total thyroidectomy alone without neck dissection.

Before surgery, the patients will first be pre-registered (included) to check that the thyroid nodule is classified cT1bT2N0 and the FNAB cytology is classified type 5 or 6 according to the Bethesda classification [51].

Surgery must be performed within 4 months of inclusion.For patients with *FNAB cytology Bethesda 6 “papillary carcinoma”*, inclusion and randomization will we performed preoperatively.For patients with *FNAB cytology Bethesda 5 “suspicious cytology”*, randomization (and validation of the inclusion) will then be performed in the operating room, after confirmation of malignancy by intra-operative frozen section analysis. For these patients, randomization will be performed online or by fax with the Trial Master program.

All patients will have Tg/LT4 measured 8 +/−2 weeks postoperatively, *before stimulation with recombinant human thyrotropin (rhTSH).*

All patients will receive, 2–4 months postoperatively, 30 mCi (1.1 GBq) ^131^I after stimulation with human recombinant thyrotropin (rhTSH) and undergo scintiscan with SPECT-CT. Neck ultrasound will be performed at the time of ^131^I administration (standard of care).

Patients will be evaluated at 8 +/−2 months post-iodine (8–14 months postoperatively or “1 year”) then yearly with neck ultrasound, unstimulated ultrasensitive thyroglobulin (usTg/LT4), and anti-Tg antibodies.

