### Intervention description

#### Randomization of patients

*Pre-registration (inclusion)* of eligible patients after signed informed consent.Surgery must be performed within 4 months of pre-registration.Quality of life (SF-36, EQ-5D, STAI) questionnaires will be completed by the patient within 1 month before the surgery.Before surgery, the patients will first be pre-registered (included) to check that the thyroid nodule is classified cT1bT2N0 and the FNAB cytology is classified type 5 or 6 according Bethesda (Appendix 2).Randomization (and validation of the inclusion)

Randomization (and validation of the inclusion) will then be performed:Before surgery for patients with malignant cytology (Bethesda 6)OR in the operating room, after total thyroidectomy without any particular dissection of paratracheal spaces and after confirmation of malignancy by intra-operative frozen section analysis for patients with suspicious cytology (Bethesda 5).

For patients with a nodule Bethesda 5, the randomization form will incude a confirmation of malignancy of the intra-operative frozen section analysis for patients with suspicious cytology Figs. 1 and 2.

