##### Radioactive iodine

All patients will have Tg/LT4 measured 8 +/− 2 weeks postoperatively, before stimulation with recombinant human thyrotropin (rhTSH).

Then, for all patients (whichever the group), radioactive iodine will be administered after 2 months but within 4 months postoperatively: 30 mCi (1.1 GBq) ^131^I after stimulation with human recombinant thyrotropin (rhTSH)

A ß-HCG test (serum or urine) will be performed before any radioiodine administration.

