##### Follow-up

All patients will have a postoperative visit within 4 months of the surgery with the surgeon to record post-op complications.

For all patients, Tg/LT4 and anti-Tg antibodies (anti-Tg Ab) measured 8 +/−2 weeks postoperatively, before stimulation with recombinant human thyrotropin (rhTSH).

At 8 +/− 2 weeks post-op before 131I:-Quality of life (SF-36) [47]-EQ-5D 3 Levels [48]-Anxiety (State-Trait Anxiety Inventory) [49]-Subjective dysphagia (measured via the SWAL-QOL questionnaire) [46]

For all patients (after 2 months but within 4 months postoperatively at the time of 131I administration:Stimulated usTg (Tg/rhTSH), anti-Tg antibodies (anti-Tg Ab)Neck ultrasoundWhole body scintiscan with SPECT performed 2–5 days after the RAI administrationQuality control of total thyroidectomy will be ensured by calculation of the % of 131I uptake, as an estimate of the size of thyroid remnant.

Further follow-up consists in:1 year after surgery (8 +/− 2 months after 131I) (primary endpoint): usTg on thyroxine treatment (usTg/LT4) with a standard ultrasensitive kit, anti-Tg Ab, neck ultrasoundYearly for 5 years (+/− 2 months after 131I): Tg/LT4, anti-Tg Ab, neck ultrasoundIf suspicious lesion (according to standardized criteria on ultrasound [52] > or = 8 mm (smallest dimension): indication for cytological examination by fine-needle aspiration biopsy (FNAB) and, for lymph nodes, for a determination the of level of thyroglobulin (Tg) in the needle washout fluidIf a suspicious lesion <8mm is visualized on ultrasound (according to standardized criteria,[52] cytology with FNAB (and Tg in the needle washout fluid) will be performed upon decision of the center’s principal investigators

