### Outcomes: Cost-utility analysis

A *cost-utility analysis* will be performed to compare total thyroidectomy to total thyroidectomy with bilateral prophylactic central neck dissection. The protocol used will be similar to the one used in ESTIMABL 1 trial and recently published in the Journal of Clinical Oncology [55]. The hypothesis is that TT alone and TTT + PND may differ in terms of the number of patients in complete remission at 1 year or in the number of patients requiring treatment of complications because of recurrent laryngeal nerve injury or hypoparathyroidism.

The horizon time will depend on the results obtained on the main criteria (1 year). If the study confirms the non-inferiority of TT versus TT + PND in terms of oncologic events, a horizon time of 1 year following the initial surgery will be considered.

Consequence will be expressed in QALYs (quality-adjusted life years). Utility score will be assessed using the EQ-5D questionnaire at baseline, 1, 3, and 5 years. QALY will be calculated by multiplying the length of time between two questionnaires by utility score.

Costs will be evaluated from the French collective perspective. Resources consumed by the patient’s management in each strategy will be collected prospectively at baseline, 1, 3, and 5 years.

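### The QALY rule does not say which utility score applies to an interval and does not hold time to the stated 12 months after surgery; the 8-week EQ-5D is collected but not listed for it

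*Protocol article*

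**What the plan says.** The rule appears in Outcomes: Cost-utility analysis and again, word for word, in Health Economics Analysis: "QALY will be calculated by multiplying the length of time between two questionnaires by utility score". Both sections fix the time points for utility: "Utility score will be assessed using the EQ-5D questionnaire at baseline, 1, 3, and 5 years". If non-inferiority is shown, "a horizon time of 1 year following the initial surgery will be considered".

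The timing of the questionnaires is set elsewhere in the article:

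- **Baseline.** Under Randomization of patients, the quality-of-life forms, EQ-5D among them, "questionnaires will be completed by the patient within 1 month before the surgery".
- **1-year visit.** Trial design places this evaluation at "8–14 months postoperatively". The window follows from the timing of radioactive iodine ("radioactive iodine will be administered after 2 months but within 4 months postoperatively") plus 8 ± 2 months.
- **An extra EQ-5D.** The Follow-up section also collects one early after surgery: "At 8 +/− 2 weeks post-op before 131I:-Quality of life (SF-36) [47]-EQ-5D 3 Levels [48". Neither cost-utility section includes it in the utility list.

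The article gives no utility value and no expected QALY difference. It describes the cost-utility protocol as similar to that of an earlier trial of the network.

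**The concern.** The rule leaves two quantities open, and both enter the QALY directly.

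**Which utility.** Two questionnaires bound an interval and give two scores, but the rule multiplies by one. On the listed schedule a 1-year horizon contains a single interval, from baseline to 1 year. With the start score, the QALY holds only pre-surgical utility and cannot show a treatment effect. With the end score, a change seen at 1 year is credited to the whole interval.

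**Which time.** The horizon is 1 year from surgery, but the stated multiplier is the gap between questionnaires. That gap can begin before surgery and end before or after 12 months. No truncation or scaling to the horizon is stated.

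QALYs are the only consequence measure named and the denominator of the incremental cost-utility ratio. If the arms are close in utility, a factor of two in the effect, or added noise of similar size to it, matters for that ratio. The planned bootstrap and one-way sensitivity analyses would carry the same QALY definition forward and would not reveal the problem.

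**Working it through.** There is no QALY figure in the plan to reproduce. Utilities below are assumptions and are shown over a range.

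**1. Length of the interval**

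Inputs: baseline 0 to 1 month before surgery; radioactive iodine 2 to 4 months after surgery; visit 6 to 10 months after iodine. Assumption: the 1-year EQ-5D is completed at the 1-year visit.

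- Shortest: 2 + 6 + 0 = 8 months
- Longest: 4 + 10 + 1 = 15 months
- Ratio: 15/8 = 1.875, from the article's windows alone

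**2. QALY for constant utility u over that interval** (u × months/12)

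| Assumed u | 8 months | 15 months |
|---|---|---|
| 0.70 | 0.47 | 0.88 |
| 0.85 | 0.57 | 1.06 |
| 1.00 | 0.67 | 1.25 |

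Over a fixed 12 months each patient would score u × 1, with no spread from timing. More than 1 QALY in the 1-year analysis needs u above 12/15 = 0.80 at the 15-month extreme.

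**3. Typical spread rather than extremes**

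Assume timing is uniform and independent within each window (widths 2, 4 and 1 months).

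- SD of interval = √[(2² + 4² + 1²)/12] = √1.75 = 1.32 months; mean 3 + 8 + 0.5 = 11.5 months
- At u = 0.85, SD of QALY from timing = 0.85 × 1.32/12 ≈ 0.094
- Contribution to the SE of the arm difference with 299 per arm = 0.094 × √(2/299) ≈ 0.008
- About 1.4% of patients would exceed 1 QALY at u = 0.85

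Variance inflation, with u independent of interval T in years and true SD s: [0.85² Var(T) + s² E(T²)]/s², where Var(T) = 1.75/144 = 0.01215 and E(T²) = 0.01215 + (11.5/12)² = 0.9306.

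- s = 0.10: (0.00878 + 0.00931)/0.0100 ≈ 1.8
- s = 0.15: (0.00878 + 0.02094)/0.0225 ≈ 1.3
- s = 0.20: (0.00878 + 0.03722)/0.0400 ≈ 1.15

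**4. Which score: listed time points only**

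Equal baseline utility (1:1 randomisation), difference d at 1 year, T = 1 year.

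- Start score: 0
- Mean of the two (area under the curve): d/2
- End score: d

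For an assumed d = 0.05 these are 0, 0.025 and 0.05 QALY. For an assumed d = 0.02 the area under the curve is 0.01 QALY, about the size of the timing SE in step 3.

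**5. With the 8-week EQ-5D added** (t = 8/52 = 0.154 year, d = 0.05)

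| Pattern of d | Start | Trapezoid | End |
|---|---|---|---|
| Present at 8 weeks and 1 year | d(1 − t) = 0.042 | dt/2 + d(1 − t) = 0.046 | 0.050 |
| Present at 8 weeks, gone by 1 year | d(1 − t) = 0.042 | dt/2 + d(1 − t)/2 = 0.025 | dt = 0.008 |

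On the listed time points the second pattern gives 0 under every reading, because the 8-week score is never used. That pattern is plausible here: the background mentions greater transient hypoparathyroidism with neck dissection.

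**The case against.** **A condensed sentence.** The article does not say actual rather than nominal time, and the stated 1-year horizon could imply scaling. A singular noun does not prescribe a step function. Interpolation and truncation may be settled in a fuller document or in the earlier trial's method, neither of which is shown. This stands in part: the sentence leaves the score open and does not order a wrong one. It is nevertheless an explicit formula, given twice, with its own list of time points. A loose reference to a similar protocol does not complete or override it.

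**The EQ-5D window is inferred.** The 8–14 months are stated for ultrasound, thyroglobulin and antibodies. The section on functional criteria and quality of life ties 1 year after randomisation to 8 ± 2 months after iodine for complications, voice and swallowing; its EQ-5D sentence gives 1, 3 and 5 years after randomisation without a window. This stands, so the 8–15 months rest on collection at the same visit. Exactly 12 months from randomisation would not restore the horizon either. Surgery may follow inclusion by up to 4 months, so a Bethesda 6 patient randomised at inclusion would complete the form 12 − 4 = 8 to 12 months after surgery.

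**Noise, not bias.** Both arms follow one schedule. A reader might infer from the open design that timing favours an arm; nothing in the document supports that. A 1-month difference in mean timing would shift the result by 0.85/12 = 0.07 QALY at u = 0.85, but that difference is hypothetical.

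**The 8-week form removes the ambiguity.** For a sustained difference it nearly does (0.042 to 0.050). For a transient one it does not (0.008 to 0.042). In either case the cost-utility sections leave that form out.

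**Conclusion.** The point holds, at minor to moderate weight. As written, the rule does not determine the QALY: on the listed time points the effect is 0, d/2 or d, given equal baselines and a single interval. Read literally, it accrues QALYs over about 8 to 15 months in place of the 12 months after surgery that the horizon names, if the 1-year EQ-5D is completed at the 1-year visit. The 1.875-fold range needs no assumed utility but is the extreme of all windows at once. The typical effect is an SD of about 0.09 QALY, under uniform timing and u = 0.85.

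Three stronger readings should be resisted:

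- That two identical patients will score 0.57 and 1.06. This needs a utility of 0.85, which the article does not give, and the window extremes.
- That the treatment effect is zero, halved or full whichever questionnaires are used. This holds only on the listed time points, without the 8-week form.
- That the trial's main conclusion is at risk. Only the secondary cost-utility outcome is affected; the primary non-inferiority test does not use QALYs.

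**What to change.** Replace the QALY sentence in both Outcomes: Cost-utility analysis and Health Economics Analysis with wording such as:

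> QALYs are the area under the EQ-5D utility curve from surgery to 12 months for the 1-year analysis, by the trapezoidal rule at actual questionnaire dates, using all collected EQ-5D including the form at 8 ± 2 weeks. The curve is truncated at 12 months; if the 1-year form is completed earlier, its value is carried to 12 months. The between-group difference is adjusted for baseline utility. Costs are counted over the same 12 months.

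Add the 8-week form to the utility time points in both sections so that they agree with Follow-up, and state when the 1-year EQ-5D is to be completed.

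The cost is wording in the health-economic analysis, with no new data collection. The downside is one carry-forward assumption for patients seen before 12 months, which can be varied in the sensitivity analyses already planned.

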#### Data collection

Resource consumption collected will concern the following direct medical costs for:Hospitalization for initial surgery, including the time in the operating room and for performing the surgeryHospitalizations for management of complications (vocal fold paralysis, hypoparathyroidism)Hospitalizations for further treatments (surgery or iodine administration)Equipment, consultations, medical or paramedical acts for management of complicationsOther direct or indirect costs that are not expected to differ between strategies will not be collected.

#### Cost valuation

Hospital stays (whatever the cause) will be valued using the French DRGs tariffs. Outpatient care costs will be valued on the basis of pricing used by the French health insurance. Tarifs of the General Nomenclature of Professional acts (NGAP), the Common Classification of Medical Acts (CCAM) will be used. Medication will be valued on the base of pricing applied by the French health insurance.

#### Cost-utility analysis

A cost-utility analysis will be performed. One-way sensitivity analyses will be performed by varying all individual costs, incidence of events, and utility variables. Probabilistic sensitivity analyses will be performed using bootstrap resampling to estimate the uncertainty around the incremental cost-utility ratio.

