### Rationale: choice of comparators

In France, total thyroidectomy with prophylactic central compartment (level VI) neck dissection as defined by the American Thyroid Association [38] is standard treatment recommended by the French Society of Otolaryngology Head and Neck Surgery,[15] whereas total thyroidectomy alone without neck dissection is recommended as standard treatment by the Francophone Association of Endocrine Surgery [19].

A simulation by the American Thyroid Association, hypothesizing a 25% difference in significant oncologic events at 7 years, with a statistical power of 80%, concluded that a randomized trial was “not readily feasible” due to the need to randomize 5840 patients [39]. This implies that both therapeutic strategies may indeed be equivalent within a small percentage, and we have therefore designed our study with a *non-inferiority statistical design with a surrogate endpoint*. This methodology (non-inferiority trial) has been clearly validated in these low-risk patients by two previous studies carried out by the same French thyroid network (TuThyRef) and published in the New England Journal of Medicine, ESTIMABL[40] and ESTIMABL2 [41]. The surrogate endpoint in the present study is the rate of excellent response as defined by the ATA,[13] or complete remission, at 1 year.

If our study confirms the non-inferiority of total thyroidectomy alone, prophylactic central compartment neck dissection could be abandoned for these low-risk patients without taking undue oncologic risks. Secondary endpoints may also show a benefit in terms of patient quality of life and of cost-utility analysis with a total thyroidectomy alone. Patients, physicians, and healthcare providers would all benefit from less-extensive surgery.

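### The bootstrap for the cost-utility result targets only the incremental ratio, which will not support a decision if the 1-year QALY difference is about 0.01 or less; net monetary benefit should be named as well.

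*Protocol article*

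**What the plan says.** The Cost-utility analysis subsection under Outcomes plans probabilistic sensitivity analyses "using bootstrap resampling to estimate the uncertainty around the incremental cost-utility ratio". The Health Economics Analysis section repeats the sentence. The only other analysis of uncertainty is one-way variation of costs, event incidences and utilities, which does not address sampling error.

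The denominator of the ratio is a difference in mean QALYs: "Consequence will be expressed in QALYs (quality-adjusted life years"). On its construction the article says "QALY will be calculated by multiplying the length of time between two questionnaires by utility score", and on timing "Utility score will be assessed using the EQ-5D questionnaire at baseline, 1, 3, and 5 years". If non-inferiority is confirmed, "a horizon time of 1 year following the initial surgery will be considered".

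No expected QALY difference, QALY SD or cost difference is given. The economic hypothesis is that the arms "may differ in terms of the number of patients in complete remission at 1 year or in the number of patients requiring treatment of complications". The Rationale for the comparators adds: "Secondary endpoints may also show a benefit in terms of patient quality of life and of cost-utility analysis with a total thyroidectomy alone".

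**The concern.** An incremental ratio has a clear meaning only when the sign of its denominator is settled. If bootstrap replicates of the QALY difference fall on both sides of zero, the replicate ratios swing between large positive and large negative values, and their sign no longer identifies the result. Taking thyroidectomy alone minus thyroidectomy with dissection:

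- a negative ratio can mean cheaper with more QALYs, or dearer with fewer QALYs;
- a positive ratio can mean dearer with more QALYs, or cheaper with fewer QALYs.

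An interval built from such a mixture pools opposite conclusions. The article presents cost-utility as one of two possible secondary gains from omitting dissection, so that claim could end up resting on an interval nobody can act on. The resampling itself is sound; the issue is the single quantity it is aimed at.

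**Working it through.** **The plan's own figure.** The article gives no number for the economic analysis. The arm size is taken from Determination of sample size, 299 per group. It reproduces if remission is 95% in both arms (a back-solved rate, not a stated one): n = (1.960 + 0.842)² × 2 × 0.95 × 0.05 / 0.05² = 298.3, rounded up to 299. The economic population is not stated. With 314 per arm (628/2) the standard errors below shrink by only about 2%, since √(299/314) = 0.976.

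**Step 1: how large might the QALY difference be?** These are illustrations, assuming a utility loss of 0.1 per affected patient:

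- Temporary hypoparathyroidism, 26% vs 10.8% in one retrospective meta-analysis in Table 1 (15.2 points), lasting 3 to 6 months: 0.152 × 0.1 × 0.25 = 0.0038 to 0.152 × 0.1 × 0.5 = 0.0076.
- An assumed 5 to 10 point difference in a complication lasting the full year: 0.05 × 0.1 × 1 = 0.005 to 0.10 × 0.1 × 1 = 0.010.

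So about 0.004 to 0.010. The listed QALY times place only baseline and 1 year within a 1-year horizon, so much of a temporary effect would go uncounted. The 8-week EQ-5D in the Follow-up section is not among the times listed for utility.

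Reaching 0.03 with baseline and 1-year utilities averaged needs a mean gap of 0.06 at 1 year. At an assumed loss of 0.1 to 0.2 per affected patient, that is 0.06/0.2 = 30 to 0.06/0.1 = 60 percentage points more affected patients. It is 15 to 30 points if the 1-year utility is applied to the whole interval.

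**Step 2: how often does the interval for the denominator span zero?** SE = SD × √(2/299), which is 0.0082, 0.0123 and 0.0164 for an assumed SD of 0.10, 0.15 and 0.20. With z = true difference / SE, the probability is Φ(1.96 − z) − Φ(−1.96 − z):

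| True QALY difference | SD 0.10 | SD 0.15 | SD 0.20 |
|---|---|---|---|
| 0 | 95% | 95% | 95% |
| 0.005 | 91% | 93% | 94% |
| 0.01 | 77% | 87% | 91% |
| 0.02 | 31% | 63% | 77% |
| 0.03 | 4% | 31% | 55% |
| 0.05 | 0% | 2% | 14% |

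**Step 3: what happens to the ratio?** Simulation with 299 per arm, assumed saving 300 euros, cost SD 1,500 euros, 400 trials of 1,000 replicates, and a percentile interval:

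- True difference 0.001: the ratio interval covers the truth in 59%, 40% and 24% of trials for SD 0.10, 0.15 and 0.20, with median width 0.37 to 0.72 million euros per QALY. The net-benefit interval (assumed 30,000 euros per QALY) covers in 93% to 95%.
- 0.005: a median of 24% to 40% of replicates have a negative denominator; median width 0.38 to 0.63 million.
- 0.01: median width 0.33 to 0.50 million.
- At 0.005 to 0.01, coverage of the ratio interval recovers to roughly 90% to 98%.

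Repeat runs moved the coverage figures by a few points.

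One simulated trial shows the shape. With true difference 0.005, QALY SD 0.15, an assumed saving of 500 and cost SD 2,000, 40% of replicates had a negative denominator and the ratio interval ran from about −532,000 to +575,000.

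**The case against.** Four points can be made on the other side.

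- **No interval method is fixed.** The text names bootstrap resampling but no percentile interval and no form of display. The same replicates could be shown on a plane or as net benefit, and nothing excludes that. The article is condensed, and it refers to an earlier trial's economic protocol that is not shown. This stands as a limit: the coverage figures test one natural reading, not a stated procedure. It does not remove the point, because the named target is the ratio, in two places, and any interval for the ratio inherits the sign problem.
- **A near-zero QALY difference is not stated.** A reader might infer that the trial itself expects the denominator to be near zero because it is built on non-inferiority. The documents do not support that. The equivalence remark and the 5% margin concern oncologic outcome and remission, equal remission does not imply equal QALYs, and the article allows for a quality-of-life benefit. A small difference is a plausible inference, no more.
- **The size depends on assumed inputs.** A reader might conclude that the interval will usually be uninterpretable. That holds at about 0.01 or less. It fails at 0.03 with an SD of 0.10, and at 0.05 for every SD shown. Severe under-coverage belongs to differences very close to zero, such as 0.001.
- **It is a secondary analysis.** True, and the non-inferiority conclusion does not depend on it.

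**Conclusion.** The point holds conditionally. The article aims its only sampling-uncertainty analysis at a ratio. If the true 1-year QALY difference is about 0.01 or less, the interval for the denominator spans zero in 77% to 95% of trials. An interval for the ratio would then be hundreds of thousands of euros per QALY wide and mix quadrants, even where its nominal coverage is acceptable. At 0.03 the probability is 4% to 55%, so the problem largely fades unless the QALY SD is large.

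These figures rest on 299 per arm from the document and on assumed values for the QALY SD (0.10 to 0.20), the QALY difference and the costs. They do not show that the planned analysis must fail. They do show that naming the ratio alone is a weak choice over a plausible range, when a better-behaved summary comes from the same replicates. This is a cheap improvement to a secondary analysis.

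**What to change.** In both Cost-utility analysis subsections (under Outcomes and under Health Economics Analysis), replace the bootstrap sentence with wording such as: *From the same bootstrap replicates, incremental costs, incremental QALYs and incremental net monetary benefit will be reported with 95% intervals over a stated range of willingness-to-pay values, together with the cost-effectiveness plane and acceptability curve. The incremental cost-utility ratio will be reported as a point estimate, with the quadrant in which it lies.*

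The ratio should not be reported only when the QALY interval excludes zero. Such a rule would make a planned summary depend on statistical significance, and at differences of 0 to 0.01 it would suppress the ratio in 77% to 95% of trials.

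The cost is a wording change, the choice of a willingness-to-pay range before the data are analysed, and a little more reporting. No new data, patients or replicates are needed.
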